##### Dissemination of study findings

The study team plans to disseminate findings among national and sub-national stakeholders through in-country dissemination events to demonstrate how, with a focus on quality in family planning, the level of satisfaction and discontinuation rate have changed. The results will be published in peer-reviewed journals and presented at both national and international conferences. Briefs indicating policy and programmatic implications will be developed and shared with the government and other stakeholders. The study will contribute to the body of knowledge that will inform decision-makers locally and globally on the determinants of contraceptive discontinuation and couple-level decision-making on the same.

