**Methods:**

This longitudinal mixed-methods study is being conducted in Migori and Kitui counties, Kenya. A formative assessment using Interviews with adolescents, older women, heterosexual couples, health care workers, and community health volunteers explored barriers to contraceptive continuation and perspectives on discontinuation utilizing a qualitative cross sectional study design. Following the formative assessment, a client-centered intervention focusing on improving quality of family planning services, including counseling, will be implemented in 10 health facilities. A 24-month prospective cohort study among women of reproductive age initiating contraception with follow-up at 3, 6, 12, and 24 months will then be undertaken to assess the discontinuation rates, examine the dynamics of contraceptive use, discontinuation and switching, and further explore barriers and enablers for contraceptive continuation and switching among the study population.

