## Study aim

In this paper, we describe a protocol for an evaluation of contraceptive continuation and method satisfaction among women and couples following interventions that are geared toward reducing discontinuation by improving the quality of family planning services offered at both health facilities and community levels. This prospective study is expected to further increase the understanding of the dynamics of decision-making among individuals and couples that influence either contraceptive continuation or discontinuation. Understanding the factors that affect the discontinuation of contraceptive use is crucial to ensuring that women and couples can attain their long-term fertility desires and have desirable reproductive health outcomes, including reducing maternal and child mortalities.

The study objectives are:
To explore reasons and factors leading to contraceptive discontinuationTo determine the contraceptive discontinuation rates at 3, 6, 12, and 24 months among women of reproductive age following a health system strengthening project that is focusing on improving quality of family planning servicesTo investigate predictors of contraceptive discontinuation and switchingTo understand barriers and enablers for contraceptive continuation and switching

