### Study design

This single group longitudinal study is being implemented in two phases employing multiple designs to respond to the objectives.

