##### Participant follow-up

Participants will be enrolled for 24 months. Data on current method use, side effects and complications, fertility intentions, satisfaction, motivation, and decision-making, including male partner involvement on contraceptive use, will be collected at five different points in time to assess the dynamics of contraceptive use, either continuation, discontinuation, or switching. Data collection will occur the following time points: at baseline and at 3, 6, 12, and 24 months (Fig. 1). At baseline, individuals who are eligible to participate and have consented to be part of the study, will complete an online questionnaire, which will be more extensive (the questionnaire is described in more detail below), prior to leaving the health facility. Participants will provide their phone contact information to enable the research team to get in touch in the subsequent follow-up period for brief interview sessions. During each follow-up interview, consent will be sought to ensure the participants are still interested in participating in the study. During each round of follow-up interviews, three attempts will be made to contact participants before a determination of loss to follow-up is made. The second and third round of interviews will take place at 3 and 6 months after baseline, because women who choose some short-term methods will require a 3-month cycle for resupply. The follow-up at 12 months will be used to determine the contraceptive continuation rate, which is the primary outcome for this study. The 12 and 24 months’ period allows comparisons with other surveys, including the DHS, that have used the same time reference to report discontinuation.

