##### Questionnaire

The baseline questionnaire has five sections: the first section covers socio-demographic characteristics, section two is on pregnancy and fertility preferences, section three is on contraception services received, section four is on the perception of the quality of care received at the health facility, and the section five is on the decision-making environment. From the pilot study conducted, we anticipate initial data collection to take 20–25 min. The follow-up questionnaires are shorter with only two sections; the first section is on contraceptive history. Participants will be asked whether they are still using their baseline contraception method, any side effects and or complications experienced, and the level of satisfaction with the method. The second section will be for clients reporting discontinuation or contraceptive switching, both closed- and open-ended questions on the timing and reasons for discontinuation or switching, including fertility intention, will be asked.

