##### Outcomes

The primary outcome of this study is the contraceptive discontinuation rate among the family planning users at 12 months. Participants will be considered to have discontinued if they report not using their baseline method during the follow-up interviews. Participants who discontinue use of the method used at the time on enrollment and initiate use of different method within one month will be considered to have switched methods. Other secondary outcome measures include discontinuation at 3, 6, and 24 months; the method information index [11] will be used as a proxy for quality of family planning counseling.

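### The plan promises to show that a quality programme changed satisfaction, but the single post-intervention cohort has nothing to measure that change against

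*Protocol article*

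**What the plan says.** - **Aim.** Study aim describes "an evaluation of contraceptive continuation and method satisfaction among women and couples following interventions". None of the four numbered objectives beneath it mentions satisfaction.
- **Promise.** Dissemination of study findings says stakeholders will be shown how, with a focus on quality, "the level of satisfaction and discontinuation rate have changed".
- **Design.** Study design states "This single group longitudinal study is being implemented in two phases". The abstract puts the intervention in the 10 facilities first and the cohort second: "follow-up at 3, 6, 12, and 24 months will then be undertaken to assess the discontinuation rates". Participant recruitment enrols women once they have received a family planning service.
- **Measurement.** Participant follow-up lists satisfaction among data that "will be collected at five different points in time", namely baseline and months 3, 6, 12 and 24. Questionnaire names five baseline sections, none of them on method satisfaction, and places the item "and the level of satisfaction with the method" in the follow-up instrument.
- **Outcomes.** The primary outcome is discontinuation at 12 months. The section continues "Other secondary outcome measures include discontinuation at 3, 6, and 24 months" and adds the method information index. Satisfaction is not named.

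**The concern.** A statement that satisfaction has changed needs something to have changed from. Tied to the quality programme and addressed to national and county stakeholders, it will be read as an effect of that programme. The only contrasts the cohort offers are between calls to the same group, all of them after the intervention began. If those contrasts are drawn among current users, women who disliked their method and stopped leave the denominator. The percentage satisfied can then climb although no woman has changed her view, and the plan's wording invites readers to credit that climb to the programme.

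**Working it through.** **1. What reference exists for each promised change?**

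| | Discontinuation | Satisfaction |
|---|---|---|
| Pre-intervention reading in the study | none | none |
| Comparator group | none | none |
| External value in the article | DHS, 31% (Sample size) | none |
| Target difference | 10 points | none |

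The sample size concerns discontinuation only. Its figure reproduces with a pooled two-proportion formula, one-sided 5%, 80% power, 31% against 21%:

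n = [1.645·√(2·0.26·0.74) + 0.842·√(0.31·0.69 + 0.21·0.79)]² / 0.10² ≈ 237

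237 × 1.5 / (1 − 0.30) = 507.9, or 508 per county and 1016 in total.

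Nothing in it bears on satisfaction. The survey figures in Background on counselling (67%, 59%, 54%) concern information given, not satisfaction. The formative phase precedes the refined intervention, but it is qualitative and purposively sampled, so it yields no level to compare with.

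**2. Is there a baseline reading?** Participant follow-up says yes. The section list in Questionnaire names none; the nearest is perceived quality of care at the facility. The two need reconciling. Either way, the baseline questionnaire is completed before the woman leaves the facility, so a baseline answer follows the intervention-era service and precedes almost all experience of the method. It cannot serve as a pre-intervention value.

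**3. How large could selection be?** Inputs from the article: the share stopping by 12 months, d = 0.31 (reference) or 0.21 (reference less the 10-point target). Assumed, because the article gives no satisfaction figure: the share satisfied at the start, s = 0.6 to 0.8; the ratio of stopping risk, dissatisfied to satisfied, r = 1 to 3; and no woman changes her view.

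- Stopping risk in satisfied women: p = d / [s + r(1 − s)]
- Share satisfied among continuers: s(1 − p) / (1 − d)

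Example with s = 0.7, d = 0.31, r = 2: p = 0.31/1.3 = 0.238, and 0.7 × 0.762/0.69 = 0.773, a rise of 7.3 points.

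| s | d | r = 1 | r = 2 | r = 3 |
|---|---|---|---|---|
| 60% | 21% | 60.0% | 64.6% | 67.1% |
| 60% | 31% | 60.0% | 67.7% | 72.0% |
| 70% | 21% | 70.0% | 74.3% | 77.0% |
| 70% | 31% | 70.0% | 77.3% | 81.8% |
| 80% | 21% | 80.0% | 83.5% | 86.1% |
| 80% | 31% | 80.0% | 86.0% | 90.3% |

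For r = 2 to 3 the apparent rise runs from 3.5 points (80% to 83.5%) to 12.0 points (60% to 72.0%). For r = 1 it is zero. The starting share is taken before anyone stops. Between month 3 and month 12, both among users, the rise would be smaller, because some stoppers have already gone by month 3.

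**The case against.** The defence has real force on several points.

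- The same women are called at 3, 6, 12 and 24 months, so change within a woman who is still using her method can be estimated, and the shift in composition shown above does not enter a paired comparison. Only the second part of the follow-up questionnaire is reserved for women who stopped or switched; the satisfaction item sits in the first part. A reader might infer that any change the study shows must come from dissatisfied women dropping out. The documents do not support that.
- A reader might also infer that there is certainly no baseline reading. Participant follow-up says there is one, and section titles are not item lists. What can be shown is a conflict, not an absence.
- The word used for secondary outcomes is inclusive, descriptive analysis of quantitative variables is planned, and a full protocol or analysis plan may hold more. The missing satisfaction outcome and analysis therefore carry little weight on their own.
- Satisfaction is absent from the numbered objectives, and reporting its level after the intervention would meet the wording of the aim. It would be too much to say that half the aim cannot be estimated.

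None of this supplies a value from before or outside the programme. Within-woman change between calls shows how views evolve with use of a method, and only in women who stay on it. It does not show what the quality programme did.

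**Conclusion.** The point holds for attribution. With one group, recruitment after the intervention-era service and no external satisfaction figure, the cohort can describe satisfaction over time but cannot show that the programme changed it. This conclusion rests on the design alone and needs no assumed number.

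The selection risk is secondary and conditional. It arises only if calls are compared among current users, and its size of about 4 to 12 points depends wholly on the assumed satisfaction shares and stopping ratios. Satisfaction could also fall as side effects accumulate, so a rise is possible, not certain.

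The primary outcome and the sample size are unaffected.

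**What to change.** 1. In Dissemination of study findings, replace the claim that satisfaction has changed with a report of its level at each time point where it is measured, and do not attribute differences to the programme.
2. State that any comparison between calls is made within the same women or on a fixed denominator, not among current users only. A fixed denominator needs a rule for counting women who stopped, switched or were lost, given the 30% attrition the plan allows for. A within-woman comparison should be labelled as applying to women who stayed on their method.
3. Reconcile Participant follow-up with Questionnaire on whether satisfaction is measured at baseline. If it is, say what the item refers to, since use of the method has barely begun.

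The cost is wording and a short table, with no new data and no change in sample size. The study gives up a claim of improved satisfaction that its design could not support.

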### Ethical considerations

Written informed consent will be obtained for all study participants. All married adolescents and those who have previously given birth will be considered emancipated/mature minors and eligible to give consent themselves. All respondents will be informed about the objectives, procedures, benefits, and risks of the study through the process of obtaining informed consent. There is some minimal risk associated with participating in the prospective cohort study especially among women taking a family planning method without the knowledge of their partners, hence, follow-up interviews might expose them. Information regarding the follow-up interview will be communicated to the participants at the time of consenting during enrolment. Participants will be asked whether they will have any concerns about their privacy regarding the follow-up interviews. During the follow-up interviews, the research assistants will establish whether the participants are in a safe environment where they can talk freely. The English questionnaire will be translated into and back-translated from Dholuo for Migori, Kamba for Kitui, and Swahili for both counties. All research assistants engaged in this study will be recruited based on prior experience in administering questionnaires. They will be trained on study design and procedures and ethical consideration, including the need for confidentiality, anonymity, consent, as well as their role as data collectors and how to complete the data collection tool. Field testing of the tool among a similar group of study participants will be undertaken prior to the study to identify potential issues that needs modification. Monitoring visits will be made by the principal investigator and co-investigators to ensure fidelity to the study protocol.

### Study status

Data collection for the formative assessment was done in May 2019 and the analysis of the results is ongoing. Refining the quality of family planning interventions using a human-centered design methodology will be done after July 2019. Enrollment of prospective cohort participants and collection of baseline data is scheduled to begin in October 2019.

## Discussion

The current evidence suggests that discontinuation can be reduced by strengthening quality of services and meeting women’s reproductive health needs [18, 19]. By implementing a project that aims on improving service delivery, some of the health system barriers that lead to discontinuation might be removed. For a country like Kenya that has seen a tremendous growth in contraceptive use and its current position in the family planning S curve [20] of high prevalence and latent growth, further growth in the mCPR modern contraceptive prevalence rate and a corresponding reduction in unmet need of family planning will likely stem from past users who have discontinued while in need of contraception.

Most studies in contraceptive discontinuation have relied on survey data based on DHS calendar information that is collected retrospectively hence prone to recall bias. By implementing a prospective cohort study, we gain deeper insights on discontinuation and method switching. Additionally, the study will shed more light on the profile of women discontinuing and further explore individual and couple-level dynamics influencing continuation and discontinuation. The information to be collected has the potential to provide empirical evidence for strategies to promote interventions that focus on improving quality of family planning and consequently improved continuation rates and satisfaction with method.

## Data Availability

Not applicable

## Abbreviations

DHS: Demographic and Health Survey
mCPR: modern contraceptive prevalence rate
USAID: United States Agency for International Development
